#### Individual level (student)

Individual participants were females aged 13-15 years of age (in Year 9 or 10) at the time of recruitment. All eligible students in the schools allocated to the intervention group were invited to participate in the VIP program. Students from both the intervention and control groups were invited to participate in a prospective study of teenage pre-conceptual health knowledge and behaviour. The participant flow is described in Figure 1.

**Figure 1 F1:**
[figure not shown]
Participant Flow

#### Timing

For the intervention arm only 5 students per school per week could participate in the program due to the availability of both School Health Nurses and Infant Simulators. To achieve the sample size required, recruitment continued over 2 years in most schools (in both trial arms). For study administration purposes and the limiting factor of having a maximum of 50 Infant Simulators operating over any one weekend the participation of the health services was staggered, with the North Metropolitan Health Service starting first, then the East and then the South. As each school completed implementation, another school started in the next health service region. In each new school year recruitment at the individual level recommenced; the study was active in each of the health services over a period of at least 3 years.

### Inclusion and Exclusion Criteria

#### Cluster level (School)

Catholic schools and male single sex schools were excluded from participating in the trial. All other schools within the metropolitan region of Perth Western Australia were approached for participation.

#### Individual level (Student)

In each of the intervention and non-intervention trial arms, all females in either year 9 or 10 were approached to participate. Male students, and female students who were pregnant or already had a child, were not actively recruited or enrolled into the study. Males were excluded from the trial due to the primary outcome being teenage pregnancy and birth outcomes along with an inability to accurately and ethically determine the male donor/contributor to a pregnancy.

### Randomisation

Randomisation was performed at the cluster level with a table of random numbers (without blocking, stratification or matching) by a researcher who was blind to the identity of the schools. After initial recruitment one government school was excluded from the intervention arm after it was detected that the study's Individual Recruitment Protocol was not adhered to. Individual participants were not blinded to their group assignment and upon giving consent were aware whether they were participating in the VIP intervention or control arm of the Trial.

### Consent

Written active consent from both a parent/guardian and the participant was required by the Ethics Committee's to access data for the longitudinal component of the research study until the participants reached the age of 20 (intervention and control arms). The consent specifically included permission for the research team to access data relating to pregnancy from hospital administrative records and abortion clinics. In a bid to maximise participation rates, four additional research staff were recruited to support School Health Nurses in their recruitment efforts. Despite best practice recruitment procedures, approved incentives and significant time and resources, the participation rates at the student level remained relatively low (Refer to Table 1). This is considered further in the discussion section of this paper.

**Table 1 T1:** Participation rates at the Individual level

Study Arm	Students approached	Consented & participated	Participation rate	Mean participants per cluster	Participant range per cluster
Intervention	2177	1267	58%	47	3-166
Non-intervention	3510	1567	45%	54	13-163

### Participant incentives

#### Cluster level (school)

No incentive other than the chance of having the program implemented at the school was provided upon recruitment. Schools were recruited into the study knowing that they would be randomised either to the intervention or non-intervention arm.

#### Individual level (student)

Students were offered a variety of nominal incentives for participation (independent of trial arm). Incentives ranged from nothing to a chocolate Freddo Frog, or a single movie ticket. The study budget did not allow for incentives; the movie tickets were donated to the research trial and the chocolate frogs were provided by the School Health Nurse at their own discretion.

### Intervention

The VIP program is a Western Australian adaption of the Reality Works^® ^Baby Think It Over Program. The adaptation was developed by the Swan Hills Division of General Practice, the Coastal and Wheatbelt Public Health Unit and the North Metropolitan Population Health Unit [11,12]. The VIP Program sought not only to delay pregnancy in the teenage years but to improve knowledge and awareness of pre-conceptual health issues that impact on low birth weight and maternal and child health outcomes. The Program is underpinned by principles of adult learning and behaviour change including Social Cognitive Theory and Stages of Change [36-39] and although it was designed as a 'stand alone' program it was written to reflect practice within the Curriculum Framework of the Western Australian Education Department and to complement and support existing health and sex education curriculum support material.

The VIP program was implemented as a standardised intervention by School Health Nurses over six consecutive days. There were four main components to the VIP Program curriculum: (1) four educational sessions in small groups of 4-5 girls; (2) a comprehensive reference workbook covering all the pre-conception health issues addressed through the program; (3) a video documentary of teenage mothers talking about their own experiences; and (4) instruction in care of the Infant Simulator which replicates the sleeping and feeding patterns of a six-week old infant.

#### 1. Small group educational sessions

All VIP participants took part in four educational sessions of 40 minutes duration (one school period) conducted in small groups of four-five girls by the School Health Nurse (SHN). In comparison, the Baby Think It Over Program does not stipulate the discipline of the person (i.e. Teacher, SHN, GP) to implement the program with the students; however it does recommend small group sessions as a supplement to the virtual parenting experience with the Infant Simulator.

The educational sessions were delivered during school time, but outside the traditional class setting; where possible they were delivered in the school health clinic. The focus of the first session was preconceptual health covering issues of contraception, STIs, drug use during pregnancy, nutrition, immunisation, pregnancy choices and health care during pregnancy. Depending on availability and resources, the first session was either delivered by the SHN in conjunction with a local "youth friendly" GP or, if the GP was unavailable, the SHN delivered the session alone with the aid of a 10 minute video of a mock preconception health visit to a General Practitioner. The second session provided an 'Introduction to Parenthood' and introduces the student workbook and asks students to plan their support network for the virtual parenting experience. The third session focused on 'Baby Familiarisation' which involved training the students how to care for the Infant Simulator. During this session students formally receive and name "their baby". Where possible this session was conducted in the last school period on a Friday so that the students were able to take "their baby" home. If school scheduling prevented this session to occur during the last school period for the week then the session was conducted during the day and the students then met the School Health Nurse after school to pick "their baby" up. At the end of the 'virtual parenting experience' a fourth and final session was conducted (generally first school session Monday morning) by the SHN, which included a debriefing and an educational component on contraception; a computerized record was downloaded from the Infant Simulator and printed for feedback and discussion with the participants.

#### 2. Student Workbook

Across the intervention period all participants completed a comprehensive reference workbook covering all the issues addressed through the program; The VIP student workbook was a significantly enhanced version of the Reality Works^® ^Baby Care Book. The Reality Works^® ^Baby Care Book included information about; how to care for and hold the Infant Simulator, car seat safety, Sudden Infant Death Syndrome and Shaken Baby Syndrome. The VIP Workbook included additional information on nutrition, exercise, immunization, contraception, body image, sexual and mental health, prevention of injury, smoking, alcohol and illicit drugs, SIDS, breastfeeding, sexually transmitted infections, post-natal depression, the economic implications of parenthood, the need for a support network, support services, and the importance of responsive care and stimulation for infant health and early brain development. Some worksheets were completed in session times while others required completion at home. In addition the Reality Works^® ^content was adapted to reflect the Australian context in relation to service providers and local regulations. Participants were able to keep their VIP Workbooks for future reference.

#### 3. Video documentary

The third component of the VIP Program is the "Talking Realities Video". The video was developed specifically for the VIP Program in conjunction with Murdoch University and the Balga Teen Family Centre (a Child Care Centre based within Balga Senior High School to help facilitate teen mothers complete their High School). The video is a documentary series of four non-judgmental interviews with teen mothers talking about their own experiences. Each mother talks about how they got pregnant, their family, friends and general public's reaction to their pregnancy and the practicalities and pragmatics of being a teen mother (i.e. not being able "party like their other friends", family support, financial and educational difficulties, and both the joys and difficulties of parenthood). The Video runs for 30 minutes but is broken into 3 sections so that the School Health Nurse could run 10 minutes of the Video in each of the small group educational sessions (to be run in sessions 2, 3 and 4).

#### 4. Virtual parenting experience

The VIP Program utilised the "Original RealCare^®^" Infant Simulators that were released by Reality Works^® ^in 1999. The Simulators replicate the sleeping and feeding patterns of a six-week old infant. It is a life-like model that is 46 centimetres long and weighs approximately three kilograms. The Infant Simulator displays infant behaviours such as different forms of crying, which are programmed to occur with a similar intensity, frequency and duration as those observed in real infants. To 'settle' the 'baby' when it cries, participants carry out various 'parenting' behaviours such as simulated breast-feeding, changing nappies and holding the infant while rocking or burping it. Crying is also triggered if the infant's head is not properly supported or if the infant is handled roughly. The 'baby' continues to cry until it has been sufficiently held and gently comforted by the participant.

The Simulators were considered too disruptive to be operated during school lessons and thus students did not care for the Simulators during school hours. Students were provided with a phone number they could call for support during the weekend if needed. During the final debriefing session, participants were presented with a 'Certificate of Achievement'.

All of the VIP Program resources were provided to each school by the research team and the Infant Simulators were purchased by and remain the property of the Trial.

### Training

Prior to implementation all administering School Health Nurses and relief nurses were trained in the delivery of the VIP Program and each nurse was provided with a Training Manual. The training also covered sessions delivered by authors A, D, E and G on research evaluation and the importance of maintaining program consistency within the practical realities of working in the school system. Research staff supported the School Health Nurses in the delivery of the program until they were able to consistently administer the program independently. In all circumstances the School Health Nurses were to deliver the program by following the student workbook, showing the videos, and programming the Infant Simulators using the same schedule (so that each participant had to go through the same program and length of running time).

### Quality Control

Research staff were in weekly communication with the School Health Nurses during the recruitment and implementation of the program, to provide support where required and to monitor and maintain program integrity.

#### SHN Manual

The School Health Nurse manual was provided to each Nurse during their initial training session. The manual was to be used as a guide and resource and to be retained for reference in their school. The Manual provided an introduction to the Program including its aims, objectives and evaluation design; Program overview and flowchart; instructions for gaining consent; an overview of each of the four program sessions; a Program checklist; Instructions for programming the Infant Simulator; and information linking the VIP program to student outcomes within the Western Australian curriculum.

#### Infant Simulator Scheduling

In all circumstances the School Health Nurse programmed the RealCare Infant Simulator using the same program, ensuring that every student had the same Simulator behaviour from Friday afternoon through to Monday morning. Utilising the Original RealCare Infant Simulator Programming Schedule the School Health Nurses were instructed to delay the program start to one hour after school providing the student some time to get home and organised. The Simulators were then to start using program 1 for day 1 (Friday), Program 2 for day 2 (Saturday), Program 3 for day 3 (Sunday), and Program 4 for day 4 (Monday). Each participant "cared" for their "baby" for 64 hours. An ID bracelet is strapped to the participant's wrist. This ID is required for the Infant Simulator to respond i.e. the Infant Simulator will only respond to and record the "care" of the participant.

### Outcome measures

#### Primary Outcome: Pregnancy (live birth or induced abortion)

A pregnancy outcome (either a live birth or induced abortion) is being determined through tracking participants via the Western Australian Data Linkage System (WADLS). The WADLS maintains a linked database of administrative health records including births and deaths, hospitalisations in private and public hospitals, and the midwives data collection, which records information on all births. The system uses a multi-staged probability method of matching based on key identifiers such as name, date of birth and address [40]. A data linkage run has been performed every three months since September 2007 and will continue until all study participants reach the age of 20 years in August 2011, although the vast majority will have turned 20 by the end of 2010.

While it is a legal requirement for all abortion providers to report induced abortions to the WA Abortion Notification System, the reporting is anonymous. The WADLS had previously only linked participants' abortion records in cases where the abortion was performed in a hospital or a facility accredited for day surgery. Such facilities are required to submit information to the Hospital Morbidity Data System (HMDS), but other clinics are not. It is currently estimated (based on data from the WA Abortion Notification System) that one-third of all abortions performed on girls under the age of 20 are in facilities which are not required to report to the HMDS (Western Australia Department of Health unpublished data). As such, the research team gained access to induced abortion data directly from these clinics. In the case of one major clinic that did not begin reporting to the HMDS until July 2007, the clinic was approached directly for access to historical records of abortions that had occurred since this Trial commencement. Relevant data on study participants has been sought from all facilities where induced abortions are performed in Western Australia and as a result of this study the information obtained from the review of the records of clinics which did not report to HMDS have now been entered into the WA Data Linkage System.

#### Secondary Outcomes (Participant knowledge, attitude and behavioural change)

Participants were assessed by a self-complete questionnaire to determine whether the program had immediate, short or longer-term impact on participant knowledge and attitudes towards pregnancy and parenting or on their health behaviours. Instruments and measures for the questionnaires were developed from a series of focus groups for the initial pilot project in conjunction with feedback from the health professionals facilitating the pilot project. Questionnaires were administered at enrolment (pre-test), at four weeks post intervention, and again at six months post intervention to glean longer term recall and risk behaviour change.

During the final debriefing (session 4), VIP Program participants (intervention arm) completed a questionnaire assessing the immediate impact of the Program. This included process measures about adherence to the Program and completion of the workbook instructional activities, change in perceptions and attitudes regarding parenting and satisfaction with the Program, and the initial response to the virtual parenting experience and health behaviours during the Program.

The pre-test and four-week post-test and six-month post-test questionnaires were completed by participants in the intervention and control arms of the study. The questionnaires included the following domains: participant demographics, life goals (e.g. importance of finishing high school, or going to university), current health behaviours (physical activity, alcohol consumption, smoking status, fruit and vegetable consumption) as well as readiness to change these behaviours; psychological distress as measured by the Kessler 10 [41]; knowledge about pregnancy and parenting; attitudes to contraception, teenage pregnancy and parenthood; sexual behaviour and contraception use. Additionally, at six months the participants were assessed on measures of impulsivity, venturesomeness and empathy using the Eysenck scales [42].

#### Infant Simulator care data

For those students participating in the intervention trial arm of the study we retained the data that was recorded by the Infant Simulator during the care period. For each student there is a record of the amount of crying time, if the Infant Simulator was shaken badly or handled roughly or in the wrong position, the number of times the head fell back (not supported correctly), the nappy was changed, breastfed, burped and rocked. These records show whether the Infant Simulator had been well cared for or neglected.

#### Maternal and Child Health Outcomes

In addition to tracking a live birth outcome via data linkage, maternal and child health outcomes are being collected for study participants who give birth during the Trial period.

Birth and early child health outcomes are obtained from the midwives data collection. Specifically, details regarding pregnancy complications, smoking status during pregnancy, plurality, gender, the child's birth weight, time to establish unassisted regular breathing, resuscitation method used (if applicable), Apgar scores at one and five minutes, estimated gestation, mode of separation (e.g. transferred or went home), adoption status, birth defects or birth trauma, any deaths of participants and still births are collected.

Maternal health and wellbeing and child health is further assessed via a post-birth interview conducted at the participant's home six months after giving birth (first child only). A strict protocol is adhered to for contacting participants. The contact details of the participants are accessed though their birth records. To organise a home interview post birth, the research team first writes to the local child health nurse and requests that the nurse contact the participant seeking their consent for interview. Once that consent is given, an interviewer from the research team with child health qualifications contacts the participant to arrange the interview. The interviewer is 'blind' as to whether the participant is from the intervention or control arm of the study. The interviewer assesses: pre-conceptual health and risk behaviours, folate supplementation, injury prevention and immunisation awareness, postnatal depression (Edinbourgh Scale) and psychological distress (K10); SIDS risk factor awareness; immunisation status; breastfeeding; awareness and uptake of health and other community supports; perceived level of support; and recall of specific VIP Program elements.

#### VIP Facilitator (SHN) satisfaction

The School Health Nurses were instrumental to the successful completion of the VIP Program in their school and their feedback on the Program content and delivery critical. On completion of Program implementation, each SHNs was interviewed by a member of the research team. The interview questionnaire included evaluation of the adequacy of VIP topics and resources, their perception of the Program impact, personal reactions to delivering the Program, and the impact of VIP on their professional relationship with the participants.

### Sample Size Calculation

The required sample size was calculated using a method that took into account the intra-cluster correlation coefficient, the anticipated effect size, the desired power, and the expected number of events. Utilising methods described by Schoenfeld and Richter [43] to calculate the required sample size, we assumed an average of 50 participants per school, a conservative intra class correlation (ICC) of 0.02 (equating to a design effect of 2), and sought to detect a 25% magnitude of difference in pregnancy rate at the 5% significance level with 80% power. Power calculations were made with a one sided test in mind as we were seeking to see a reduction in the number of pregnancies in the intervention compared to the non intervention group (a result of no difference or indeed an increase in pregnancy rate would be interpreted as the VIP Program failing in its primary outcome). The expected birth rate, abortion rate and pregnancy rate in the control group were estimated from WA Department of Health figures specific to the age and postcode of residence that matched the study population (6% expected to have live birth, 10.8% abortion, and thus 16.8% known pregnancy). The minimum required number of participants was estimated to be around 1,300 per study arm. It was expected that over the follow-up period the magnitude of clustering effects would decline as the students leave school and the prevalence of risk behaviours such as unprotected sexual activity become less influenced by school peers. Loss to follow-up was not considered to be a significant factor in this research design as the primary outcome measures are being obtained via the Western Australian Data Linkage System (WADLS). Any participant who has a birth or an induced abortion in a hospital or day surgery facility within the state of Western Australia should be tracked through the WADLS. Participants having a birth or abortion outside of Western Australia between the age of recruitment and the time they turn 20 would not be identified by the record linkage system; however it is assumed there would be no difference in rate of migration out of the State between the trial arms.

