### Planned analyses for the Primary Outcome

#### Primary outcome - pregnancy

For live births, the birth date of the baby will be used as the outcome date. For abortions, the recorded admission date for abortion will be used. For overall pregnancies we will estimate the due date of a pregnancy for abortion cases by adding 6 months to the abortion date, as the majority of induced abortions take place in the first trimester. Where more than one pregnancy outcome is detected, the date of the first event will be used. Kaplan-Meier survival analyses will be undertaken for these primary outcomes. To adjust for clustering by school and potential confounding variables, the data will be analysed using Cox proportional hazards regression, using the Lin and Wei robust sandwich estimate of the variance-covariance matrix. All analyses will be undertaken using SAS or SPSS.

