Recruitment bias becomes a threat to the external validity if there are systematic differences in the characteristics of participants in the intervention and control arms that are associated with the exposure or outcome variables. Unfortunately, the study was unable to collect information from the students who did not participate or the parents who failed to provide consent. Therefore we can only anticipate differences between participants and non-participants based on the best available evidence. In general epidemiological studies, participants are more likely to be of higher socioeconomic status, employed, married and of better health status. Further, in studies of risk behaviours, those engaged in those behaviours are less likely to participate [49] The requirement for active parental consent has been associated with the lesser representation of ethnic minorities, students having problems at school and students already engaged in or at risk of problem behaviours [52,54]. So while the study cannot control for systematic differences between participants and non-participants, it can statistically control for potential baseline differences between the intervention and control groups. The following data has been collected by the Trial to investigate and control for potential confounders: socio-economic status, family type, whether the participant had ever had sexual intercourse, had ever had responsibility for caring for a baby, reported importance and intention of going to University or further education, level of psychological distress, and smoking, drug and alcohol use. These variables were measured at the time of entry into the Trial. Additionally each participant's educational attainment data has been linked to the Trial data to enable controlling for academic success.

In conclusion although the pragmatic nature of the trial and the low participation rates will provide some complexities for the analyses, the results will have international significance and advance the evidence to inform school based teen pregnancy prevention programs.

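### The 16.8% control pregnancy rate is an upper bound used as the expected rate, and the stated 80% power is not reached at about 1,300 per arm even at that rate

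*Protocol article*

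**What the plan says.** The Sample Size Calculation section of the protocol article "sought to detect a 25% magnitude of difference in pregnancy rate" "at the 5% significance level with 80% power", and adds: "Power calculations were made with a one sided test in mind". It assumes 50 girls per school and an intra-class correlation of 0.02, which it equates to a design effect of 2, and arrives at about 1,300 participants per arm.

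The control rate is built as "6% expected to have live birth, 10.8% abortion, and thus 16.8% known pregnancy". Its source is "WA Department of Health figures specific to the age and postcode of residence that matched the study population".

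Under Outcome measures, the primary outcome is a live birth or an induced abortion. Under Planned analyses for the Primary Outcome, each girl contributes one event: "Where more than one pregnancy outcome is detected, the date of the first event will be used".

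Table 1 (Consent section) shows that 58% of approached girls took part in the intervention arm (1,267) and 45% in the control arm (1,567). On studies of risk behaviours, the Discussion says that "those engaged in those behaviours are less likely to participate". It also links active parental consent to fewer at-risk students. It adds that nothing was collected on girls who did not take part, so differences can only be anticipated.

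**The concern.** Power in a time-to-event analysis depends on the number of girls with at least one event. Two features of the planning rate push that number up.

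- **Overlap.** A girl with both a birth and an abortion counts in the 6% and in the 10.8%, but once in the analysis. If the rates count events rather than girls, repeat events inflate the sum further.
- **Population.** The rates were matched on age and postcode, not on consent. The article itself expects consenters to carry less risk, yet gives no lower rate.

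Checking these leads to a third matter: whether 1,300 per arm gives 80% power at 16.8% at all. The sample-size section says that no difference would count as the program failing on its primary outcome. A reader who takes the 80% at face value would give a null result more weight than the design supports.

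**Working it through.** **Inputs from the article:** one-sided 5%; 80% power; 25% reduction, taken as hazard ratio (HR) 0.75; control rate 16.8%, hence 0.75 × 16.8% = 12.6% in the intervention arm; design effect 1 + 49 × 0.02 = 1.98, stated as 2; 1,300 per arm planned; 1,267 and 1,567 enrolled.

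**1. The plan's own figure.**
Schoenfeld events = 4 × (1.645 + 0.842)² / (ln 0.75)² = 299.
Participants per arm = 299 × 2 / (0.168 + 0.126) = 2,034, not 1,300.
Other readings of the same inputs also miss 1,300: HR 0.732 (equivalent to a risk ratio of 0.75) gives about 1,735, and a comparison of two proportions gives 1,756.
Among the variants tried, 1,300 appears only with a two-sided test and no design effect: 380 / 0.294 = 1,293. The article does not say that this is what was done.

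**2. Power at the stated rate.**
Power = Φ(0.2877 × √(D × f × (1 − f) / 2) − 1.645), where D is the expected number of girls with an event and f the intervention share.
- 1,300 per arm: D = 1,300 × 0.294 = 382, f = 0.5. Power = Φ(1.988 − 1.645) = 63%.
- Enrolled: D = 0.168 × (1,567 + 0.75 × 1,267) = 423, f = 1,267 / 2,834 = 0.447. Power = Φ(2.080 − 1.645) = 67%.

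The two-proportion method gives 69% and 72%.

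**3. Effect of overlap.**
Share with at least one event = 6% + 10.8% − share with both. The article gives no joint figure.
- No girl with both: 16.8% (the strict upper bound).
- Independence (assumed): 0.168 − 0.06 × 0.108 = 16.15%.
- 30% of girls with a birth also having an abortion (assumed): 0.168 − 0.018 = 15.0%.
- Every girl with a birth also having an abortion (arithmetic floor): 10.8%.

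**4. Effect of volunteering.** No figure is given. As an illustration, a rate 20% lower is 0.8 × 16.8% = 13.4%. At 1,300 per arm, expected events fall from 382 to 306.

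**5. Power over the range** (one-sided 5%, HR 0.75, design effect 2; every rate below 16.8% is an assumption):

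| Control rate | Power, 1,300 per arm | Power, enrolled | Needed per arm for 80% |
|---|---|---|---|
| 16.8% | 63.4% | 66.8% | 2,034 |
| 16.15% | 62.0% | 65.3% | 2,116 |
| 16% | 61.6% | 65.0% | 2,136 |
| 15% | 59.3% | 62.6% | 2,278 |
| 14% | 56.8% | 60.0% | 2,441 |
| 13.4% | 55.3% | 58.5% | 2,543 |
| 12% | 51.4% | 54.5% | 2,848 |

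**6. Splitting the shortfall at 1,300 per arm.** From 80% to 63.4% is about 17 points and arises before the rate is touched. Independent overlap adds 63.4 − 62.0 = about 1.5 points. The assumed 20% volunteer effect alone adds 63.4 − 55.3 = about 8 points.

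**The case against.** The other side has several good points.

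- **Overlap is minor.** Independent overlap costs about 1.5 points. In a trial truly powered at 80% (2,034 per arm) it would leave 78.6%. This stands.
- **Enrolment exceeded the plan.** With 2,834 girls against about 2,600, the planned 382 events are still expected down to a control rate of 382 / (1,567 + 0.75 × 1,267) = 15.2%. This stands for the event count, but not for 80% power, since 382 events never gave 80% under the stated inputs.
- **The definition of the rates lies in an unseen source.** They could be mutually exclusive first outcomes, and then 16.8% is right. This cannot be excluded, but the article presents them only as a birth rate and an abortion rate.
- **The volunteer effect has no size.** The Discussion reports general tendencies and already names low participation as the main limitation. The sample also departs from its postcodes in other ways (Catholic schools excluded; 51 of 57 schools government), so the net shift is not known. This stands: the 14% and 12% rows are illustrations.
- **Clustering may weaken.** The article expects this over follow-up. At 16.8%, 80% power needs a design effect of at most 382 / 299 = 1.28 at 1,300 per arm. The article gives no figure for the decline and plans with 2.
- **Recruitment is over**, and precision can be read from the confidence interval. That limits the consequences but does not make the stated power correct.

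A reader might also infer from the first-event rule that girls with both a birth and an abortion are expected. It is a conditional rule and covers two births or two abortions equally.

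**Conclusion.** The point holds in two parts of unequal weight.

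The lesser part concerns the rate. 16.8% is an upper bound used as an expectation, unless the two components are mutually exclusive first outcomes. It also comes from area figures applied to girls whom the article expects to be at lower risk. The direction follows from the text; the size does not.

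The greater part concerns the power. The stated one-sided 5% test, 25% reduction (as HR 0.75) and design effect 2 give about 63% at 1,300 per arm and 67% at the enrolled numbers, even at 16.8%. Reading the 25% as a difference in proportions raises these to 69% and 72%, still short of 80%.

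Two stronger readings are tempting and not supported. The first is that the inflated rate is why 80% is missed. Most of the gap is there at 16.8%, because 1,300 does not follow from the stated inputs. The second is that the true rate is at most about 16.2%. That figure assumes independence; with negatively associated or exclusive outcomes the rate lies between 16.15% and 16.8%.

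**What to change.** In the Sample Size Calculation section:

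1. Describe 16.8% as an upper bound on the share of girls with at least one event, and say whether the 6% and 10.8% are per-girl, per-event or first-outcome rates. Do not replace it with a ceiling of about 16.2%.
2. State that the rates are area figures, that consenting girls may fall below them, and that the size of the difference is unknown.
3. Restate power for the 1,267 and 1,567 enrolled, with the one-sided 5% test and the design effect of 2. Use the arm-blind pooled number of girls with at least one event from the quarterly linkage runs held since September 2007. Enter that total directly as D. The pooled proportion is not the control rate: under HR 0.75 a 16.8% control rate implies 423 / 2,834 = 14.9% pooled. Runs before all girls reach 20 give an incomplete count and should be labelled so.
4. If the pooled count is not used, give a range labelled as assumption: control rates of 16.8%, 16%, 14% and 12% give about 67%, 65%, 60% and 54%.
5. Reconcile 1,300 per arm with the stated inputs, or state which inputs produced it.

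The cost is one recalculation and revised wording. The stated power becomes less favourable. No extra participants are needed.
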